### Data analysis

The primary objective is to assess the impact of AV biofeedback on breathing regularity and image errors; the section that follows details the metrics to be utilised for the primary objective.

Breathing motion regularity is quantified as the root mean square error (RMSE) in displacement and period [13, 21, 24, 34]. A breathing signal is separated into its individual cycles and an ‘average’ waveform is calculated using a Fourier series fit. Figure 4 illustrates an example breathing trace, its separation into cycles, and its average waveform.

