### Objectives

This clinical trial will recruit 75 lung cancer patients across 7 radiation oncology departments testing the following objectives:

Primary objective: In a prospective multi-institutional randomised clinical trial we will test the hypothesis that AV biofeedback will significantly improve breathing regularity and reduce medical imaging errors for lung cancer patients undergoing imaging and treatment procedures during radiotherapy.

Secondary objectives will involve patient-specific and department-specific objectives:

Patient-specific objectives are to evaluate the impact of AV biofeedback by:Quantifying the proportion of patients for whom breathing is more regular with AV biofeedback,Quantifying the variability in breathing motion throughout a course of treatment,Quantifying the improvement in image quality with AV biofeedback,Evaluating the patient experience through a perception of care survey,Developing indications and contra-indications for the use of AV biofeedback,Quantifying the differences in image-guided radiotherapy (IGRT) shifts during treatment, andRecording toxicity outcomes for up to 12 months after treatment has been completed.

Department-specific objectives are to evaluate the impact of AV biofeedback on clinical testing by:Quantifying any practice changes (e.g. margin reduction),Quantifying the impact on workflow using the AV biofeedback device through time-motion studies,Evaluating the operator and clinician confidence in the AV biofeedback device’s reliability and clinical efficacy through a technology-impact survey,Quantifying the system robustness through hardware and software fault reporting, andPerforming system quality assurance, sharing the results through web-based uploads and provide feedback for QA improvement.Our methodological framework will be based on the widely used Technology Acceptance Model (TAM) [25, 26]. The TAM gives qualitative scales for two specific variables, perceived usefulness and perceived ease of use, which are fundamental determinants for user acceptance.

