### Sample size and power calculation

The statistical considerations for this study are largely based on a previous study conducted at Virginia Commonwealth University (VCU) on 24 lung cancer patients [23, 29]. Prior to this multi-institutional clinical trial, the VCU study was the largest AV biofeedback investigation, recruiting a total of 26 lung cancer patients, however, 2 patients dropped out due to not being treated with radiotherapy or rapid worsening of disease, and so their data was not collected. In the VCU study 109 breathing sessions were performed comparing AV biofeedback to free breathing, of which, 87 sessions (80 %) demonstrated more regular breathing with AV biofeedback. Framing this is in a more clinical relevant way: irregular breathing motion exacerbates the systematic errors (Σ) arising from motion image artefacts and variations between the planned and treated anatomy, as well as random errors (σ) from day-to-day variations in the treated anatomy [30, 15, 31]. To combine systematic and random errors and estimate the margin contribution due to breathing irregularity we will use the van Herk method [32]: margin = 2.5Σ + 0.7σ, incorporating the respiratory components of systematic and random errors. A clinically significant difference in clinical improvement due to AV biofeedback has been determined to be a margin calculation of less than 5 mm. This magnitude of reduction was elected as clinically significant because this is the same magnitude of displacement attributed to contributing to significant artefacts and errors during radiotherapy procedures as detailed in AAPM Task Group 76 [4]. From this van Herk calculation, in the VCU study there were 14/24 patients with margins <5 mm with AV biofeedback, while only 5/24 for free breathing.

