In this proposed study, to get a more accurate indication of the proportion of patients with reduced margins calculated using the van Herk method we have designed an exploratory phase II randomised study examining the potential impact of an AV biofeedback system in regulating breathing in patients receiving radiation therapy for the treatment of lung cancer. Without the AV biofeedback system, it is conservatively estimated that approximately 40 % of patients naturally exhibit regular breathing (margin component below 5 mm). Increasing this proportion to 60 % using the AV biofeedback system would be clinically worthwhile. Based on Simon’s design, [33] a sample size of 50 patients receiving the AV biofeedback system will have at least 80 % power with 95 % confidence to rule out a regular rate of 40 % in favour of a 60 % rate. To minimise patient selection bias and provide an estimate of regular breathing from a contemporary control, the proposed design will be a randomised phase II with a 50 patients receiving the intervention and 25 receiving current standard of care. Patients will be randomised in a 2:1 ratio, with 2/3 of the patients being recruited into the AV biofeedback (intervention) arm and 1/3 in the free breathing (control) arm as illustrated by Fig. 3. 2:1 randomisation is appropriate as within the interventional arm there is a screening procedure where only patients whose breathing is more regular with AV biofeedback use this system for their imaging and treatment procedures. Patients will be stratified by treating institution and for treatment intent (palliative vs. radical) to ensure similar balance in the arms across the sites. As the study is not powered for formal comparisons between the groups, estimates of the proportion of patients which do not experience irregular breathing will provide information as to whether further investigation is warranted.

Assuming a contamination and dropout rate of no more than 10 %, this study will require that 75 + 8 = 83 patients be recruited (the 10 % value was based on the 2/26 patient drop-out rate in the VCU study).

Patients at each institution will be treated per department protocol with no additional constraints on dose, fractionation, immobilisation or image guided procedures. Results will be adjusted for institution (using a fixed effect) to account for differences between institutions.

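### The sample size rests on the proportion with a margin component below 5 mm, but the Data analysis section lists three other measures as the primary-objective metrics, and none of them has a power basis

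*Protocol article*

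**What the plan says.** **Sizing.** The Sample size and power calculation section uses "margin = 2.5Σ + 0.7σ, incorporating the respiratory components of systematic and random errors" and takes 5 mm as the clinically relevant limit. It equates regular breathing with falling below that limit: "patients naturally exhibit regular breathing (margin component below 5 mm". The design figures follow: "it is conservatively estimated that approximately 40 % of patients naturally exhibit regular breathing", and "Increasing this proportion to 60 % using the AV biofeedback system would be clinically worthwhile". Fifty intervention patients are said to give at least 80 % power with 95 % confidence. The stated purpose of the trial is "to get a more accurate indication of the proportion of patients with reduced margins calculated using the van Herk method". The section also says that the trial is not powered for formal comparison of the groups, and that the estimated proportion without irregular breathing will inform whether to investigate further. The main Discussion section repeats this basis for the decision.

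**Primary-objective metrics.** The Data analysis section announces that "the section that follows details the metrics to be utilised for the primary objective". It continues: "Breathing motion regularity is quantified as the root mean square error (RMSE) in displacement and period". It then describes the NCC-based method for finding 4D-CT artefacts. The margin does not appear there.

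**Objectives and power claim.** The Objectives section states the primary objective as a test of significantly better breathing regularity and fewer imaging errors. The patient-specific secondary objectives include "Quantifying the improvement in image quality with AV biofeedback". The Discussion paragraph of the abstract says that the study is powered for both breathing regularity and image quality.

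**The concern.** The article uses regular breathing in two ways. In the sample size section it is a yes/no property of a patient, margin component below 5 mm. In Data analysis it is two continuous measures of the breathing trace. These are related but different quantities, and nothing in the article converts one into the other. The 40 % and 60 % rates therefore cannot be applied to the measures declared for the primary objective.

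Imaging error is in a weaker position still. It is half of the primary hypothesis, appears again as a secondary objective, and is claimed in the abstract to be powered, yet no calculation concerns it.

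An analyst who follows Data analysis literally would report a primary result on measures for which the trial was not sized, and would leave out the one endpoint that has a target and an error rate. A reader of the abstract would credit the image-quality result with power that the article does not show.

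**Working it through.** **1. Reproduce the stated power.** Inputs from the sample size section: n = 50, null rate 0.40, target rate 0.60. Assumption: 95 % confidence means one-sided 0.05, since sidedness is not stated. The check is a single-stage exact binomial test that takes the smallest r with P(X ≥ r | 50, 0.40) ≤ 0.05.
- r = 26: alpha 0.0573, too large.
- r = 27: alpha 0.0314, and power P(X ≥ 27 | 50, 0.60) = 0.844.

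The claim of at least 80 % power holds. The smallest single-stage n that reaches it is 42. A Simon two-stage search gives a total of 46 (optimal) or 39 (minimax), so 50 is enough. If 95 % confidence meant one-sided 0.025, the rule would be at least 28 of 50, with alpha 0.016 and power 76.6 %, below 80 %.

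**2. Does that calculation carry over to the Data analysis metrics?**
- The margin combines systematic and day-to-day random error, in millimetres, and is cut at 5 mm. With no random error at all, a systematic error of 5/2.5 = 2 mm reaches the limit.
- RMSE in displacement measures how the cycles of a breathing pattern depart from the average waveform of that same pattern. RMSE in period is in seconds. Neither has a cut-off.
- NCC compares edge slices at adjacent couch positions.

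No formula or threshold ties any of these to a margin below 5 mm. The earlier 24-patient study is cited for counts only: 87 of 109 sessions more regular with guidance, and margins below 5 mm in 14/24 (58 %) with guidance against 5/24 (21 %) without. It supplies no mean, difference or SD for RMSE or NCC.

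**3. Is there a between-arm basis?** For the sized endpoint, 40 % of 25 against 60 % of 50, by normal approximation:
- pooled proportion = (10 + 30)/75 = 0.533
- null SE = √(0.533 × 0.467 × (1/25 + 1/50)) = 0.1222
- alternative SE = √(0.24/25 + 0.24/50) = 0.12
- two-sided power = Φ((0.20 − 1.96 × 0.1222)/0.12) = Φ(−0.33) = 37 %

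This agrees with the article's own disclaimer.

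For a continuous measure, power = Φ(d/√(1/25 + 1/50) − 1.96) = Φ(d/0.245 − 1.96), where d is an **assumed** standardised difference, because the article gives none:

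| d (SD units) | Power, two-sided 0.05 |
|---|---|
| 0.4 | 37 % |
| 0.5 | 53 % |
| 0.6 | 69 % |
| 0.8 | 90 % |

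The difference detectable with 80 % power is (1.96 + 0.84) × 0.245 = 0.69 SD. Whether the trial is powered for RMSE or NCC therefore depends entirely on a figure that the article does not state.

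**The case against.** The strongest reply is that the deciding endpoint is in fact fixed. The sample size section commits to the van Herk calculation prospectively, gives the limit and both rates, and ties the decision on further work to a single proportion. The Discussion section does the same. The margin is introduced there as a clinical expression of breathing irregularity, so its absence from Data analysis is largely a fault of placement and labelling. The study also calls itself exploratory, and rules on combining measures or on multiplicity may sit in a full protocol or analysis plan that is not shown.

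Much of this stands, and it limits the point. A reader might infer that success could be declared on whichever of four measures turned out well, and might attach an inflated false-positive rate to that. The documents do not support this. No section says that each measure is tested at 5 % or that any one suffices, the primary hypothesis joins its two parts with *and*, and the decision is tied to one proportion. Nor are the two meanings of regularity shown to be incompatible; they are different and unmapped.

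What the reply does not remove is the contradiction in the text. Data analysis says that it gives the primary-objective metrics and omits the sized one, and the abstract claims power for image quality without any calculation behind it. An unseen analysis plan could choose between the two statements but could not follow both.

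**Conclusion.** The concern holds as a mismatch between stated passages. The only power and confidence in the article belong to the proportion with a margin component below 5 mm in the intervention arm. There the sizing is adequate: 84 % power at exact alpha 0.031, assuming a one-sided 0.05 test in a single stage. None of it applies to RMSE in displacement, RMSE in period or NCC, which Data analysis presents as the primary-objective metrics. For those three no power can be stated. Under assumed differences of 0.4 to 0.8 SD it would run from 37 % to 90 % in a two-sided 50 against 25 comparison, so the abstract's claim is unsupported rather than shown to be false.

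The finding does not extend to an inflated error rate or to a free choice of winner.

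**What to change.** - In Data analysis, name the proportion with margin component below 5 mm as the primary endpoint, tested in the intervention arm against 40 %, and state the rule and its sidedness. For example, success at 27 or more of 50 has exact one-sided alpha 0.031 and 84 % power at 60 %.
- Report RMSE in displacement, RMSE in period and NCC as secondary measures, without a power claim.
- List image quality once, as a secondary objective, and word the primary hypothesis to match.
- Limit the power statement in the abstract to the margin endpoint.
- Bring the abstract, Objectives, Sample size and power calculation, Data analysis and Discussion into line. This includes the disclaimer on formal comparisons, which refers to the groups in the sample size section but to the stratified groups in the Discussion.

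The cost is text only: no added patients and no added data. The real concession is that imaging error and RMSE lose primary status, although both are still reported. If the sponsor wants one of them to stay primary, the alternative is to size the trial on that named measure, with a stated difference and SD and a rule for combining measures, which may change the number of patients.

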**Fig. 4 Fig4:**
[figure not shown]
Example of breathing motion trace (left) then separated into individual cycles with the average waveform shown as the red dashed curve (right)

RMSE will be calculated as detailed by Venkat, et al., (2008),[13] but will be outlined here for clarity. For a breathing pattern comprised of *n* individual breathing cycles, where each cycle in the phase domain can be written as *X* = {*x*_1_, *x*_2_, …, *x*_360_} and the average waveform of these cycles can be written as *Y* = {*y*_1_, *y*_2_, …, *y*_360_}, the RMSE in displacement is calculated as: 1$$ RMSE\  in\  displacement = \frac{{\displaystyle {\Sigma}_{All\  Cycles}}\sqrt{{\displaystyle {\Sigma}_{i=1\dots 360}}\frac{{\left({x}_i\mathit{\hbox{-}}{y}_i\right)}^2}{360}}}{n} $$

The period of each of the $$ n $$ breathing cycles, in seconds, can be written as *P* = {*p*_1_, *p*_2_, …, *p*_*n*_}, with the period of the average waveform expressed as *Period*_*mean*_, the RMSE in period is calculated as:2$$ RMSE\  in\  period = \sqrt{\frac{{\displaystyle {\varSigma}_{i=1\dots n}}{\left({p}_i\mathit{\hbox{-}} Perio{d}_{mean}\right)}^2}{n}} $$

The impact of AV biofeedback on 4D-CT image quality will utilise an automated method of image artefact identification developed by Cui, et al., (2012), [35] but will be outlined here for clarity. The method is based on the similarity between edge slices at adjacent couch positions *A* and *B*; the edge similarity between slice *A* and slice *B* is expressed by the normalised correlation coefficient (NCC). Deviations from standard NCC, representing normal anatomical changes between edge slices, signify the presence of an image artefact. Cui, et al., (2012) reported good agreement of their method with the assessment of two observers.

## Discussion

This clinical trial marks an important milestone in breathing guidance studies as it will be the first randomised, controlled trial providing the most comprehensive evaluation of the clinical impact of breathing guidance on cancer radiation therapy to date. Based on the structure of previous investigations, and taking into consideration the increase in scope of this study, the authors have designed a multi-institutional, randomised, phase II, stratified clinical trial to test the hypothesis that audiovisual biofeedback breathing guidance will significantly improve breathing regularity and reduce medical imaging errors for lung cancer patients undergoing imaging and treatment procedures during radiotherapy. While patients will be stratified by treating institution and for treatment intent, the study is not powered for formal comparisons between the these stratified groups; estimates from the current proposed study of the proportion of patients which do not experience irregular breathing will provide information as to whether further investigation is warranted. Further to this, objectives such as determining the indications and contra-indications for the use of audiovisual biofeedback, evaluation of patient experience, radiation toxicity occurrence and severity, and clinician confidence will shed light on the design of future phase III clinical trials.

## Abbreviations

AV biofeedback: Audiovisual biofeedback
HREC: Human Research Ethics Committee
PET: Positron Emission Tomography
MRI: Magnetic resonance imaging
ANZCTR: Australian New Zealand Clinical Trials Registry
RPM: Real-time position management
IGRT: Image-guided radiotherapy
QA: Quality assurance
TAM: Technology acceptance model
ECOG score: Eastern cooperative oncology group score
VCU: Virginia Commonwealth University
